### Qualitative data

Focussed thematic analysis will be utilised, as in a previous study evaluating experiences of treatment [58, 59] which compared participants’ experiences in a non-randomised trial of intensive and weekly CBT for OCD. Constant comparison method [60] will be used to delineate themes and sub-themes relating to participants’ experiences and attitudes towards treatment.

Two researchers will independently code three transcripts to help identify and discuss alternative interpretations of the data [61]. An analytical framework will be constructed around the perceived value, acceptability and feasibility of the treatment, which will be applied to the remaining transcripts, with themes and subthemes refined as necessary. Deductive codes will be supplemented with inductive codes to reflect the emergent priorities and concerns in the data. Ideas about themes and their relationships will be recorded in theoretical memos and discussed amongst our Project Service User Advisory Group. The computer programme QSR N-VIVO will be used to process the transcripts, enabling coding and retrieval of a large volume of narrative data.

## Monitoring

### Composition of the coordinating centre and trial steering committee

The Trial Management Group (TMG) comprises FC, LP, BC and VL. An independent trial steering and data monitoring committee will be established to examine the clinical progress of trial participants and the conduct of the trial. The group comprises two clinicians, one statistician and one expert by experience. This will meet soon after the beginning of recruitment and then every 6 months to oversee the trial, check data and adverse events; a trial report is prepared in advance. A charter for the group is available from the corresponding author.

### Patient and public involvement

Patients were involved in advising on the design of the study. A patient advisory group (PAG) comprising 4–6 women with lived experience of perinatal mental health problems will be set up to advise on the study and will meet approximately annually.

### Adverse event reporting and harms

Participants will be carefully monitored throughout treatment by asking them for relevant information at each contact. Data will be collected from participants on potential adverse effects including pregnancy outcomes and prematurity.

Adverse events will be monitored and recorded, including the mental and physical health of the mother and any pregnancy-related events. Should participants deteriorate clinically in terms of significantly increased symptoms of anxiety or depression, or an increase in risk to themselves or others, then the intervention will be stopped and a referral made to specialist perinatal services and/or other services as clinically appropriate.

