#### Time-intensive CBT

This will comprise 8–10 h (depending on the disorder) of one-to-one CBT delivered in 4–5 sessions over 1–2 weeks, delivered at the earliest convenient point between 12 and 36 weeks of pregnancy. The CBT treatment will be delivered by a high-intensity cognitive behaviour (HI CBT) therapist, which is standard practice within IAPT services. Two follow up sessions of 1 h each will then be offered by the HI CBT therapist which will include one in late pregnancy (33–35 weeks’ gestation) and one at 1m postpartum.

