#### Standard weekly CBT (treatment as usual)

Standard weekly CBT will comprise 8–10 hours (depending on the disorder) of one to one CBT on a one hour per week basis. This is termed ‘high intensity’ CBT in IAPT services and will be offered to all women who participate in the trial and are randomised to standard weekly CBT. The CBT treatment will be delivered by a High Intensity Cognitive Behaviour (HI CBT) Therapist, which is standard practice within IAPT services. Two follow up sessions of one hour will then be offered by the HI CBT Therapist which will include one in late pregnancy (33–35 weeks’ gestation), one at 1m postpartum.

Treatments may take place via phone or video link using Microsoft Teams, depending on current restrictions due to the Coronavirus.

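### Asking about harms at each treatment contact gives the weekly arm about twice as many enquiries during active treatment, so transient events may be under-recorded in time-intensive CBT

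*Protocol article*

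**What the plan says.** Under Adverse event reporting and harms, the protocol article states: "Participants will be carefully monitored throughout treatment by asking them for relevant information at each contact". The next sentence adds: "Data will be collected from participants on potential adverse effects including pregnancy outcomes and prematurity". That second sentence gives no time point. The section also counts the mother's mental and physical health among the events to be recorded.

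The contact schedules are set out by arm under Details of interventions.

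- Time-intensive CBT: 8–10 hours of "one-to-one CBT delivered in 4–5 sessions over 1–2 weeks". Afterwards, "Two follow up sessions of 1 h each will then be offered by the HI CBT therapist", one at 33–35 weeks' gestation and one at 1 month postpartum.
- Standard weekly CBT: "Standard weekly CBT will comprise 8–10 hours (depending on the disorder) of one to one CBT on a one hour per week basis". The same two follow-up sessions are offered.

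Both arms then have the outcome assessment at 3 months postpartum (Table 1; Questionnaire data). The sections on baseline assessment and questionnaire data also say that anxiety, depression and disorder-specific scores are taken at each point of contact. No harms enquiry on a calendar common to both arms is stated.

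**The concern.** When events are found by asking, the number found depends on how often one asks. Here the frequency of asking is a feature of the allocated treatment. At the same true event rate, the arm asked more often will tend to record more short-lived or minor events. Temporary deterioration is exposed in the same way: a brief rise in a symptom score can be seen only if a score is taken while it lasts, and the weekly arm has about twice as many in-treatment scores.

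The direction matters. The Abstract says that time-intensive CBT has not been trialled in pregnant women, and the trial is meant to inform the design of a full-scale trial. The steering and data monitoring committee checks adverse events every 6 months. Under-recording in IN-CBT would make the new format look safer than it is, and an enquiry scheme that depends on arm could be carried into the definitive trial. Analysis cannot recover events that were never elicited.

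**Working it through.** The article states no number of enquiries, so there is no figure to reproduce. The counts below come from the two intervention descriptions and Table 1.

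**Check on the reading of the schedule.** Ten hours of treatment plus two one-hour follow-ups make 12 hours, and 0.6 × 12 = 7.2. This matches the 7.2 of 12 hours in progression criterion (iii).

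**Number of contacts, IN-CBT v weekly**, pairing the 8-hour courses and the 10-hour courses:

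| Contacts counted | 8-hour course | 10-hour course | Ratio weekly/IN-CBT |
|---|---|---|---|
| Active treatment | 4 v 8 | 5 v 10 | 2.0 |
| Plus two follow-ups | 6 v 10 | 7 v 12 | 1.67–1.71 |
| Plus 3-month assessment | 7 v 11 | 8 v 13 | 1.57–1.63 |

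Mixing course lengths in the second row gives outer limits of 10/7 = 1.43 and 12/6 = 2.0.

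**Gap between the last active session and the 33-week follow-up.** Entry is allowed from 12 to 25 weeks.

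- Start at 12 weeks: IN-CBT ends by week 14, a gap of 33 − 14 = 19 weeks. Weekly CBT ends at week 20–22, a gap of 11–13 weeks.
- Start at 25 weeks: IN-CBT ends by about week 27, a gap of 6 weeks. Weekly CBT ends at week 33–35, so there is no gap.

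**What this could do to counts.** The following is an illustration on assumptions that are not in the article: events fall evenly from randomisation to 3 months postpartum; an event is recorded only if a contact follows within a recall window r; there are 5 v 10 sessions starting one week after randomisation, with the IN-CBT sessions spread over two weeks; shared contacts are at 34 weeks, 1 month and 3 months after a birth at 40 weeks (weeks 34, 44.3 and 53).

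For entry at 20 weeks and r = 4 weeks, over 33 weeks of observation:

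- IN-CBT covers 3 weeks up to the last active session, then 4 weeks before each shared contact: 3 + 4 + 4 + 4 = 15, and 15/33 = 0.455.
- Weekly covers 10 + 4 + 4 + 4 = 22, and 22/33 = 0.667.
- Ratio of events captured, IN-CBT/weekly: 15/22 = 0.68.

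The same calculation for entry at 16, 20 and 24 weeks gives:

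| Recall window | Capture ratio IN-CBT/weekly |
|---|---|
| 1 week | 0.46–0.50 |
| 4 weeks | 0.68–0.83 |
| 8 weeks | 0.79–1.0 |
| 13 weeks | 0.95–1.0 |
| Remembered until the next contact | 1.0 |

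The imbalance is large for events soon forgotten and vanishes for events that a woman will still report months later.

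**The case against.** The strongest reply is that the events the section names, pregnancy outcomes and prematurity, are memorable, cluster around birth, and will be picked up at postpartum contacts that are identical in the two arms. That stands, and it limits the point to transient or minor events and temporary deterioration.

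A second reply is that no comparison of adverse events between arms is planned. None of the seven listed feasibility parameters is an adverse-event count, harms are not a progression criterion, and the analysis is mainly descriptive. That also stands. What is affected is descriptive counts, committee reports and what is handed on to the full trial, not a test.

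A third reply is that this is an article, and that forms, recall periods and tabulation belong in the full protocol or the committee charter. This is fair for those details. But the rule for eliciting harms is stated, and following it as written gives unequal enquiry. If the full protocol already has a common checklist, the article needs only to say so.

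A reader might also infer stronger things that the text does not support:

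- That the weekly arm is observed for longer overall. Only the active phase is longer; both arms share contacts at 33–35 weeks, 1 month and 3 months postpartum.
- That events after an early IN-CBT course go unasked. They are asked about late, at the 33–35-week session, and no recall limit is set.
- That a 19-week gap is typical. It is the early-entry extreme, and the weekly arm has a gap of 11–13 weeks from the same start.
- That the weekly arm is bound to record more events of every kind. The working shows no difference for events that are remembered.

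**Conclusion.** The point holds in a limited form. As written, the plan makes harms enquiry depend on arm: 2.0 times as many enquiries in the weekly arm during active treatment, and about 1.6–1.7 times overall. Transient adverse events and temporary deterioration may therefore be under-recorded in IN-CBT, in the direction that favours the new format. The size of any distortion cannot be read from the article, because it depends on how long women remember an event. The illustration runs from roughly half the weekly arm's capture with one-week recall to equal capture with full recall. The counts assume that all planned sessions are attended and that harms are asked about at every one. This is a worthwhile and cheap improvement, not a flaw that threatens the trial's feasibility aims.

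**What to change.** Keep asking at every contact for individual safety. In addition, use one identical adverse-event and pregnancy-event checklist in both arms at the three contacts they share: the 33–35-week session, the 1-month postpartum session, and the 3-month postpartum assessment. Each should ask about the whole period since the previous common point, and the first about the period since randomisation. At 3 months the blind research assistant should complete it before the qualitative interview, which the Blinding section expects to reveal allocation. Base any harms summary by arm on these reports, and list events found only at other treatment contacts separately.

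Scheduled enquiries feeding the summary then number 3 v 3, a ratio of 1.0. The cost is a short form at existing contacts and a change of wording, with no added visit or staff. The drawback is longer recall for minor events, so some will be missed in both arms. The therapists who hold the first two contacts also know the allocation, so only the 3-month report is blind.

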### Dissemination plans

Results of the trial will be fed back to participants via a newsletter.Findings from the study will be published in a series of high-quality peer reviewed papers. These will include journals targeted at academics, CBT practitioners, perinatal specialists and health service managers.Study results will be presented at academic and service user led conferences as well as conferences for managers. Examples would be the British Association for Behavioural and Cognitive Psychotherapies conference, Marce conference, Maternal Mental Health Alliance conference.Findings from the study will be disseminated to service user groups in perinatal mental health and for anxiety disorders and umbrella organisations such as the maternal mental health alliance.Clinical approaches developed from the study would be disseminated in clinical skills workshops and training for existing and new CBT therapists. These would take place in IAPT and specialist perinatal settings.

### Protocol version and amendments

This publication is based on protocol number and date ADEPT Protocol v3_03.06.20.

## Discussion

There is a need for effective and accessible treatments for pregnant women with anxiety disorders. This study will be the first to examine the use of time-intensive CBT in pregnant women. It is designed to assess questions of acceptability and feasibility, in order to inform the design of a full-scale RCT. The study data will inform this using both quantitative and qualitative data to assess feasibility outcomes. Time intensive CBT has the potential to be an effective and time efficient intervention for women with anxiety during pregnancy. It is designed to be delivered in existing psychological services and could therefore potentially be rolled out widely across the NHS.

### Trial status

Recruitment started in September 2019 and is expected to be completed by end September 2021.

## Data Availability

Not currently applicable. Participant level data will not be available due to the small and potentially identifiable dataset.

## Abbreviations

ADSUS: Adult service use measure
CADAT: Centre for anxiety disorders and trauma
CBT: Cognitive behaviour therapy
CI: Chief investigator
CTS-R: Cognitive therapy scale-revised
CTU: Clinical trials unit
DSM-V: Diagnostic and statistical manual of mental disorders fifth edition
GAD: Generalised anxiety disorder
GAD-7: Generalised anxiety disorder scale-7 items
HI: High intensity
IES: Impact of events scale
NHS: National health service
NICE: National institute for health and care excellence
IAPT: Improving access to psychological therapies
OCD: Obsessive-compulsive disorder
OCI-R: Obsessive compulsive inventory-revised
PAG: Patient advisory group
PBQ: Postpartum bonding questionnaire
PHQ-9: Patient health questionnaire
PRAQ: Pregnancy-related anxiety questionnaire
PTSD: Post-traumatic stress disorder
RCT: Randomised controlled trial
SCID-V: Structured clinical interview DSM-V
SLaM: South London and Maudsley NHS Trust
SPIN: The social phobia inventory
SPSS: Statistical package for the social sciences
WSAS: Work and social adjustment scale
TMG: Trial management group
